### Sample size estimation

G *Power (v. 3.1) was used to estimate the sample size needed to test hypotheses 1, 2, 3 and 5. A mixed model using treatment as a between-subjects factor (MBHC, MBHC-VR, and WL) and time as a within-subjects factor (pre, inter, post, and follow-up) will be tested. Interaction effect was powered. The sample size was estimated taking as a reference a small difference in perceived stress between MBHC with vs without VR-assisted meditation in university students [5]. With an alpha criterion of .05 and a small effect size (Cohen’s d^2^ = .08), to achieve a minimum of 80% power, a minimum sample size of 174 participants will be needed. Assuming an attrition rate, based on complete dropout of approximately 20% [5], the final sample needed will include at least 210 university students (i.e., 70 participants in each of three groups).

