### Data analysis

#### Quantitative data analysis plan

The data analysis plan will be conducted following four steps. R Software [66] will be used for all data cleaning and statistical tests with a significance level of alpha < .05.

*Data preprocessing*. Demographics and clinical records will be described at baseline by means of frequencies (percentages) or means (SD). Independent *t*-test for continuous data and chi-square test (*χ*^2^) for categorical data will be conducted to confirm that there were no demographic or clinical differences between groups at baseline. Following the CONSORT guidelines [38], Intention-To-Treat analysis will be performed using Maximum Likelihood estimation via Expectation Maximization imputation [67]. The procedure suggested by Hair et al [68] will be followed to handle missing data: 1) the types of missing data and percentage of missing will be analyzed to ensure that none exceed the recommended thresholds; 2) Little’s MCAR (Missing Completely At Random) test will be used to assess whether the missing data is completely random; and 3) sensitivity analysis will be performed to determine the impact of missing data on the results of a study, comparing the main outcomes between completers and imputed values.

*Multilevel Modelling (MLM)*. First, efficacy of MBHC and MBHC-VR compared to WL control condition will be analyzed by using MLM. Multilevel analysis enables the control of variance associated with random factors without the need for data aggregation. Variance across participants, instructor of each group, and subgroup of delivery (i.e., edition) will be modeled as random effects. Group (i.e., MBHC, MBHC-VR, and WL) and time (i.e., pre-intervention, inter-session, post-intervention, and 3-month follow-up) will be modeled as fixed effects. Analyses will be conducted via restricted maximum likelihood estimation (REML), which provides a less biased estimate of variance components with small sample sizes [69]. The group x time interaction will be used to study the trajectories of each group throughout the intervention and to determine whether the between-group differences are maintained over time.

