*Structural equation model (SEM)*. We will use the lavaan R package to implement structural equation models (SEM) by to investigate whether there are any significant mediators of training outcome. Results will be reported following the recommendations in Raykov et al. [78]. Cases with missing values and outliers will be detected using Mahalanobis distance. Multivariate and univariate normality assumptions will be tested using Mardia’s test and Kolmogorov-Smirnov’s test with the MVN R package [79]. If non-normality is found, Satorra-Bentler scale test and standard bootstrapping will be used. Model fit will be assessed using several criteria [80]: 1) a ratio of *χ*^2^*/gl<2* suggests an acceptable fit; 2) A RMSEA size below .06 suggests a well-fitting model; 3) a comparative fit index (CFI) above .95 indicates a good fit; 4) a SRMR of less than .09 also indicates a good fit; and 5) The chi-square statistic provides a conventional measure of model fit.

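### Bootstrapping of the mediation model (Hypothesis 6) is triggered by non-normal variables, but an indirect effect is non-normally distributed even when the variables are normal

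*Protocol article*

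**What the plan says.** Hypothesis 6 (Protocol article, Hypotheses) predicts that the psychological functioning variables carry the effect of training, against control, on occupational balance and mental health. The Quantitative data analysis plan tests this by structural equation modelling in lavaan, looking for significant mediators.

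The distributional rule has two parts. First: "Multivariate and univariate normality assumptions will be tested using Mardia’s test and Kolmogorov-Smirnov’s test with the MVN R package". Then: "If non-normality is found, Satorra-Bentler scale test and standard bootstrapping will be used". Model-fit criteria follow. The article does not say how an indirect effect is tested, or what interval it is given, when normality is not rejected. The general level is "statistical tests with a significance level of alpha < .05", with sidedness not stated.

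Under Sample size estimation, the calculation was made to "estimate the sample size needed to test hypotheses 1, 2, 3 and 5". Hypothesis 6 is not among them.

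**The concern.** The rule hangs two tools with different purposes on one trigger. The Satorra-Bentler correction adjusts the model chi-square for non-normal data, so a normality test of the variables is a sensible guide to it. Bootstrapping an indirect effect answers another need. The effect is a product, a×b, where a is the path from group to mediator and b the path from mediator to outcome. At modest sample sizes and small-to-medium paths, the estimate of that product is skewed and peaked even if mediator and outcome are exactly normal. Passing Mardia and Kolmogorov-Smirnov therefore says nothing about whether a normal-theory z for a×b is adequate.

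The stake is missed mechanisms, not false ones. The normal-theory z errs on the conservative side, and Hypothesis 6 was given no sample size of its own, so power there may already be short.

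**Working it through.** **The plan's own figure.** The minimum of 174 is for the group-by-time interaction. It reproduces with three groups, four time points, alpha .05 and f = √.08 / 2 = 0.141 at a within-person correlation of 0, and equally with f = 0.10 at a correlation of 0.5 (power 80.4% in both). The article does not state the correlation. It gives no figure for mediation.

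**Inputs**
- N: 210 × 0.8 = 168 after the stated 20% dropout, or the stated minimum of 174.
- Comparison: both programmes against waiting list, 2:1, from the 1:1:1 allocation.
- Alpha .05; two-sided is my assumption.
- Paths: none in the article. Assumed a from 0.28 to 0.80 SD and b from .14 to .50 for power, residual SDs 1, direct effect 0, normal errors.

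**Why the z test is conservative.** Write z_a = a/SE(a) and z_b = b/SE(b). The delta-method statistic is

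z_ab = ab / √(a²·SE(b)² + b²·SE(a)²) = z_a·z_b / √(z_a² + z_b²),

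which is always below the smaller of z_a and z_b. If the two are equal, each must reach 1.96 × √2 = 2.77 before z_ab reaches 1.96.

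At N = 168, SE(a) = 1/√(168 × 2/3 × 1/3) = 0.164 and SE(b) = 1/√168 = 0.077.
- a = .4, b = .20: z_a = 2.44, z_b = 2.59, z_ab = 1.78. Each path is expected to pass 1.96, but their product is not.
- a = .4, b = .50: z_a = 2.44, z_b = 6.48, z_ab = 2.29. With one strong path the penalty is small.

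**Simulated power with normal errors** (600 to 2,000 trials per cell; a range is given where repeat runs differ)

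| N | a | b | Delta-method z | Percentile bootstrap | Difference (points) |
|---|---|---|---|---|---|
| 168 | .28 | .20 | 12–15% | 28–29% | about 15 |
| 168 | .40 | .20 | 26–30% | 47–49% | about 20 |
| 168 | .40 | .25 | 40–41% | 59–60% | about 20 |
| 168 | .50 | .20 | 41–42% | 61% | about 19 |
| 174 | .39 | .20 | 29.6% | 48.7% | 19 |
| 174 | .50 | .26 | 63.2% | 78.8% | 16 |
| 168 | .28 | .50 | 37% | 42% | 5 |
| 168 | .40 | .50 | 63–65% | 68–69% | about 5 |
| 168 | .50 | .40 | 81–82% | 86–87% | about 5 |
| 168 | .60 | .50 | 95% | 96% | 1 |
| 174 | .80 | .39 | 99.3% | 99.5% | 0 |

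At other sizes the largest difference found was 20 points at N = 116 (one programme against waiting list), 21 at N = 140 and 24 at N = 210.

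**Type I error, z against bootstrap**
- a = b = 0 (N = 174): 0.1% and 0.1%.
- a = 0, b = .14 (N = 174): 0.3% and 2.2%.
- a = 0, b = .4 (N = 168): 3.0% and 5.2%.
- a = 0, b = .6 (N = 168): 4.7–4.9% and 5.9%.
- a = .8, b = 0 (N = 168): 2.8–4.3% and 5.6%.
- a = 0, b = .39 (N = 116): 2.9% and 6.6%.

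**How often the trigger would fire at N = 174**
- Mardia: 8% with exactly normal mediator and outcome, 49% with skewness about 0.5, 97% with skewness about 1, and 95% if the binary group variable is included.
- Kolmogorov-Smirnov (Lilliefors form, rounded scores): 19% for a normal score with SD 8, 72% with SD 4, 97% at skewness 0.5, 100% at skewness 1.

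A 20-point conditional loss therefore averages 20 × 0.03 = 0.6 points if the trigger fires 97% of the time, and 20 × 0.81 = 16 points if it fires 19% of the time.

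**The case against.** Four points on the other side carry weight.

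1. **The default test is not stated.** A reader might infer that the plan prescribes a delta-method z. It does not: the article names no Sobel test, z or interval, and the sentence on bootstrapping sits beside the Satorra-Bentler test and the fit criteria. The z test is an inference from the conditional wording, since the condition would have no purpose if bootstrapping applied anyway. The choice of interval could be left to a fuller plan, but the condition itself is printed here, and that is what needs changing.

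2. **The trigger will often fire.** The scales are bounded sums of Likert items and some will be skewed. For those models the plan already does what is asked and the loss is nil. A reader might take 20 points as the typical loss; it is the upper end, for models that pass the check and have small-to-medium paths.

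3. **The path sizes are assumed.** The gap is largest with b around .20 to .25 and shrinks to about 5 points with b of .4 to .5. The article gives no basis for choosing between these.

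4. **Mixed tests across mediators.** A reader might infer that the pre-test decides, mediator by mediator, which mechanism is called significant. The article does not say so. It includes a multivariate test, so one skewed outcome could bring in bootstrapping for every mediator in that model.

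None of these rescues the trigger. They limit how much it costs.

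**Conclusion.** The concern holds as a minor point. A normality test on the variables is the wrong condition for bootstrapping an indirect effect. If models that pass it fall back on the delta-method z, power against a percentile bootstrap is lower by about 0 points for large paths, about 5 for b of .4 to .5, and about 20 for a of .4 to .5 with b of .20 to .25. This assumes normal data, N of about 168 to 174, a 2:1 comparison and no direct effect. The average loss over all models will be smaller, by an amount that depends on how skewed the scores turn out to be and cannot be fixed from the article. The z test does not create false mechanisms, mediation lies outside the sample-size calculation, and the efficacy comparisons do not depend on it.

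**What to change.** State that every indirect effect will be tested with a percentile-bootstrap 95% confidence interval (for example 5,000 resamples), whatever the normality tests show. Keep Mardia and Kolmogorov-Smirnov only to decide whether the Satorra-Bentler correction is applied to model fit.

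The cost is one sentence and trivial computing time, with no new data. The statistical price is a type I error that can run slightly above 5% (about 5 to 7% in simulation) when one path is zero and the other sizeable. If the normality tests would have rejected anyway, the change alters nothing.

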#### Qualitative data analysis plan

Data analysis will be carried out following the modified grounded theory approach [81]. Interviews will be transcribed verbatim and checked for accuracy. They will be imported into the MAXQDA program [82], from which the analysis will be performed. A thematic index (coding) will be built, and it will be applied independently to the first transcripts by three researchers. The following process will be followed: 1) selection of the most significant phrases; 2) initial grouping of significant phrases into categories and themes; 3) creation of identification codes for categories and themes; 4) validation of the categories and redefinition where appropriate.

Subsequently, all researchers will again check the adequacy of the interpretation of data to ensure that data allocation is systematic and verifiable. Finally, a conceptual map will be made, and the data will be interpreted, explaining the association patterns.

## Discussion

The present randomized clinical trial has been designed to evaluate and compare the effects of MBHC and a MBHC-VR on university students’ OB and mental health. For this purpose, a wide variety of indicators related to occupation (OB, eating and sleep habits, and physical activity), mental health (anxiety, depression, stress, academic stress and burnout), and psychological functioning (emotional regulation, psychological flexibility, acceptance, mindfulness-trait, self-compassion, and life satisfaction) will be evaluated in three randomized groups (i.e., MBHC intervention group, MBHC-VR intervention group, and WL control group) and four moments (i.e., pre-intervention, inter-session, post-intervention, and 3-month follow-up). The analysis of the variables will be carried out through retrospective questionnaires, EMA, and focus groups.

Although there are previous MBPs targeting university students, to our knowledge, this is the first time that mindfulness supported by VR will be explored by mixed methodology and EMA. In addition, an important difference is that the present study considers the impact on occupation, that is, how mindfulness affects the activities of daily life of the students.

This study also presents several strengths. The study design is based on previous similar clinical trials, although some improvements were introduced. Since mindfulness itself is a complex construct to evaluate, different questionnaires that evaluate processes related to this construct will be used (FFMQ-SF, SCS-SF, DERS, AAQ-II), in order to obtain more complete data. A social desirability scale (M-C SDS) is also included, since in the psychometric assessment of mindfulness this type of effect may occur (participants may try to show a more positive or more "mindful" image of themselves, even when this self-representation does not reflect their true reality) [87]. Besides, the EMA has been added to the traditional retrospective evaluation, a methodology that evaluates the change on a day-to-day basis, and at the very moment in which the events occur, which improves the ecological validity and eliminates the possible memory bias associated with the retrospective assessment instruments. On the other hand, the qualitative methodology, based on focus groups, allows a better understanding of the change process, as well as knowing what the experiences, difficulties, preferences, and satisfaction after the programs. This mixed methodology can provide more extensive and in-depth information on the MBIs, as it will help to know not only the efficacy and the long-term effects of the interventions, but also their acceptability. Feedback from participants will allow the research team to improve the programs in order to better meet the needs of the target population.

Furthermore, this study addresses an occupational engagement-based perspective. That is, variables related to daily occupations are included, with the intention of improving university students’ meaningful and balanced participation in daily occupations. To our knowledge, research on mindfulness and OB in university students is limited.

The gender perspective is also considered. In this sense, not only the biological sex of the participants will be collected, but also the gender with which they identify. Both variables will be taken into account in the phase of statistical analysis of the data, in order to verify their relationships with all the variables evaluated and the effect of the MBIs on them.

In this study, special attention is also paid to the possibility of adverse effects associated with the practice of meditation, as evidenced by previous studies [64, 88, 89]. In anticipation of this, the participants will communicate to the research team any difficulty or symptomatology that may arise, in order to attend to and solve these events as quickly as possible and, if necessary, refer the participant to the specialized psychological services available at the university. Likewise, participants will also report possible adverse effects during and/or after VR exposure. In the MBHC-VR group of this research, VR with neutral and pleasant contents will be used in all sessions for a time between 10 and 15 minutes, favoring adaptation to the exposure and minimizing possible adverse effects.

It is also worth mentioning that the programs will be implemented by a multidisciplinary professional group with extensive experience in university education and highly qualified in MBIs. In this sense, the team is made up of occupational therapists, psychologists, physiotherapists, mindfulness experts and university professors’ experts in teaching and research.

In terms of feasibility, face-to-face interventions will be carried out in groups of about 15 people, who can be attended simultaneously, thus being a low-cost community mindfulness program for university students. If the MBHC programs designed for this study are effective, one of the advantages is that their applicability can be extended to other universities. Also, the materials and procedures will be available to the educational and scientific community. Thus, the range of effective interventions available to address university students’ mental health will be expanded.

The present trial can also contribute to expanding knowledge on personalized treatments. Baseline characteristics of individuals have started to be used as predictive factors of differential response to intervention strategies. This study will allow identifying individuals within the included sample that will benefit more from utilizing one condition relative to the other. It will also allow to establish moderating mechanisms of efficacy.

In short, and from the point of view of clinical practice, it is expected that with the proposed intervention university students will learn to relate in a healthier way with their mental processes, so as to improve their OB and their psychological well-being.
